**Intervention:**

*Experimental group:* 40 sessions, 5/week, during 2 months, 1 hour experimental intervention in addition to 1 hour control motor rehabilitation.[^42^](#_ENREF_42)

*Control group Intervention:* Conventional motor rehabilitation (2-hour, 40 sessions).

*Rest Period:* A 10-minute rest period will be provided after 1 hour session to all the study participants. The subjects will be allowed to have water or light snacks during the break.

*Assessment Sessions: 02 pre-, 01 post- intervention and 01 follow-up (1-month)*

**Experimental Intervention:**

**T**ask-based and **MAG**nified **M**irror Therapy for **U**nilateral **S**patial **N**eglect (T-MAGUSN)

The experimental intervention will comprise of the following components -

- 1. Task-based upper limb mirror therapy (20 minutes x 40 sessions)
  2. Task-based lower limb mirror therapy (20 minutes x 40 sessions)
  3. Magnified mirror therapy (10 minutes x 40 sessions)
  4. Task-based parasagital plane visual feedback mirror therapy (10 minutes x 40 sessions)
     1. Task-based upper limb mirror therapy

The protocol guidelines will be followed as per our previous work[^34^](#_ENREF_34) on upper limb motor recovery using task-based mirror therapy. However, necessary modification in terms of USN as an objective of the intervention will be carried out. A wooden mirror box / frame of size (LxBxH = 30x18x40 inches; reaching height and breadth) will be used. Various objects such as pegs, pyramids, blocks, clay, ball, U-clips, balls and coins will be utilized to provide the mirror therapy. The textured objects[^24^](#_ENREF_24) will also be provided to provide the multi-sensory awareness. The subject will be made to sit close to a table on which the mirror box / frame will be placed vertically at the mid sternum level. The less-affected upper limb will be placed in front of the mirror to visualize the image while the affected limb will be placed inside the mirror box. Subject could perceive the image of the less-affected limb as the affected limb. By observing the image of the less-affected upper extremity as a projection over the affected limb, an illusion will be created *(figure 1).* The tasks will be provided with an objective to perceive the body part, movement and object in the ipsilesional space as the illusion of the contralesional space. The objects will be reached for, grasped, lifted, placed and manipulated in different spatial planes (Forward/backward, superior/inferior, medially/laterally, diagonally). The therapist will instruct for the direction and may locate the object in the desired plane by standing in front of the patient. The movements of all the joints (shoulder, elbow, forearm, wrist, hand and fingers) will be utilized in view of the associated motor impairment. The number of tasks, joints, repetition, speed, time and resistance will be considered as parameters for grading the intervention.

*
[figure not shown]
*

*Figure 1: A left hemiparetic subject with USN performing wiping task by the right upper limb; experiencing the illusion for the left upper limb (in the contralesional space) created by the functional use of the right side.*

- - 1. *Task-based lower limb mirror therapy*

For the lower limb mirror therapy, the protocol will be followed as per our previous study.[^35^](#_ENREF_35) A short-sitting mirror frame measuring 24 x 72 inches will be used with a provision of the mirror to be tilted in the sagittal plane to view the mirror at an acute angle, between 75 and 85 degrees. The arrangement enabled maximum mirror perception of the moving limb without having any possible sight of the body part. Another frame measuring 36 x 48 inches will be used the long-sitting MT. The subject will receive task-based movements such as pedaling, wiping, and shifting pillow were provided on the less-affected side in front of the mirror while hiding the affected limb *(figure 2).* The activities will be graded as described for the upper limb program.

**
[figure not shown]
**

*Figure 2: A left hemiparetic subject with USN performing Rocking-board activity by the right upper limb; experiencing the illusion for the left lower limb (in the contralesional space) created by movement of the right side.*

- - 1. *Magnified mirror therapy*

To provide the intervention a magnified (2-3X) mirror *(figure 3)* will be utilized. The task-based therapy, guidelines as described at *above 1*, will be followed. The hand and finger manipulation using various meaningful objects will be used by the less-paretic hand to provide the illusion for the paretic hand. The subject will be asked to visualize the magnified body part and objects minutely and then manipulate the objects. The movements will be performed indifferent spatial planes. The number of tasks, repetition, speed, time and resistance will be considered as parameters for grading the intervention.

[figure not shown]

*Figure 3: A magnified mirror*

- - 1. *Task-based parasagital plane visual feedback mirror therapy*

A mirror frame will be positioned vertically on the less-affected side with a therapist standing behind it. The mirror frame will be held parallel to the sagittal plane so that its right edge will be close to the patient’s paretic shoulder. The subject will be asked to turn his head and eyes to look into the center of the mirror so he could clearly see the mirror reflection of the people/ objects that are on the left side. To ensure that the patient is looking in the mirror, the therapist (standing behind the mirror) will enquire about holding of the mirror. A second therapist standing on the patient’s paretic side will hold a block or cone and move towards the subject so that it is well within the reach of the subject’s non-paretic hand but entirely within the neglected (paretic) visual field – about 8 inches below and to the paretic side nose. The therapist will then enquire about the object and ask the patient to reach for the item. Similarly, the objects will be positioned and enquired and asked for the reach and manipulation in different locations. The number of objects, repetition, speed, time and resistance will be considered as parameters for grading the intervention.

**Control intervention**

In addition to the conventional motor rehabilitation,[^42^](#_ENREF_42) the control group will be provided following intervention[^43^](#_ENREF_43) for the USN rehabilitation for a dose match (2- hour) program –

- Mirror frame will be placed in front of the patient while he will be performing activities of daily living, ambulation and motor activities (unilateral and bilateral) in order to draw attention to the neglected side.
- Mid-line crossing activities – unilateral and bilateral
- Scanning, puzzle, trail making, drawing activities

**Outcome measures:**

**Primary measures**

**Unilateral Spatial Neglect**

1. ***Line Bisection Test (LBT)***

There are three 20-cm horizontal black lines in the LBT. One line is on the right of the page, one line is in the center, and one is on the left. The patients will be instructed to mark the center of each line. Errors will be measured in centimeters from the true midline. Leftward errors will be indicated with negative numbers and rightward errors will be indicated with positive numbers. The cutoff score for unilateral visual neglect will be considered as an error of more than 1.4 cm left or right. It is a reliable and valid measure of USN and commonly used measure in stroke studies.[^27^](#_ENREF_27)

1. ***Letter Cancellation Test (LCT)***

A single-target Letter Cancellation Test (LCT) will be the main outcome measure to assess USN requested to cross all O’s on an A4 paper taped on the table and aligned to their sagittal midline. Each paper contained 40 O’s (20 in the contralesional and 20 in the ipsilesional visual field, respectively left and right) and 425 distractor letters. USN has been defined as an asymmetry between the LCT omissions in the contralesional (left) and ipsilesional (right) visual field of at least 2. It also possesses adequate psychometric properties and usually applied in stroke investigations.[^33^](#_ENREF_33)

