USN is a strong predictor of poor motor recovery and functional performances among the stroke subjects.[^12^](#_ENREF_12) The impaired ability has significant physical, social, and emotional implications. Considering the International Classification of Functioning, Disability and Health, USN undoubtedly affects body structure and function that subsequently leads to activity limitation and participation restriction.

Cognitive rehabilitation has been recommended as one of the important areas of stroke research that warrant independent synthesis of evidence generated in LMICs.[^13^](#_ENREF_13) Further, globally, research on cognitive impairment after stroke is at an earlier stage of evolution than research in motor recovery.[^14^](#_ENREF_14) The studies to enhance cognitive deficits among stroke survivor are recommended as a top first question for research.[^15^](#_ENREF_15) The proposed study may be applicable to the *National Stroke Registry Program (NSRP) / National Programme for Prevention and Control of Cancer, Diabetes, Cardiovascular Diseases and Stroke* (NPCDCS) in terms of rehabilitation services to control and prevent disability for comprehensive management of stroke patients.[^16^](#_ENREF_16)^,^ [^17^](#_ENREF_17)

[^15^](#_ENREF_15)

1. **Literature review:**

USN is a frequent and disabling impairment after stroke. The terms unilateral neglect, visuospatial neglect, hemineglect and spatial neglect are used interchangeably. Although the USN usually occurs on the contralesional side in the right brain damage, the deficit may be observed on the ipsilesional side as well as among subjects with the left brain damage.[^11^](#_ENREF_11)^,^ [^18^](#_ENREF_18)^,^ [^19^](#_ENREF_19) The functional performance of an individual with USN gets hampered. Most of the investigations have been focused on the impairment and management of upper limb functions. In addition to this, the USN affects lower limb functions such as locomotion and stair climbing. The post-stroke subjects with USN are at more risk of falling in comparison to the subjects without USN.[^20^](#_ENREF_20)^,^ [^21^](#_ENREF_21) The functional ambulation including stair climbing gets more impaired than the stroke subjects without USN.[^20^](#_ENREF_20)^,^ [^22^](#_ENREF_22) Further, USN has been identified as a key element that may impede upper limb and lower limb recovery.[^12^](#_ENREF_12)

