**Inclusion Criteria:**

- Age: 20 to 80 years
- Both male & female
- First episode of unilateral stroke (as defined by WHO)
- Ischemic or hemorrhagic stroke
- 1 to 36 months after the stroke onset
- Hemiparesis (right or left) (as assessed by Fugl-Meyer assessment[^38^](#_ENREF_38) upper extremity subsection: 0 to 66)
- USN (defined as an asymmetry between the Letter cancellation task omissions in the contralesional (left) and ipsilesional (right) visual field of at least 2 letters)[^33^](#_ENREF_33)
- Normal visual abilities (with or without glasses)
- Muscle tone: Modified Ashworth scale 1 to 2

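### Line bisection error is signed by page side although either hemiparetic side is eligible, so its group contrast shrinks by 1 − 2p; letter cancellation rows are also labelled by page side

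*Protocol*

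**What the plan says.** **Scoring.** Under Outcome measures, the Line Bisection Test (LBT) is a primary measure, with three 20-cm lines and errors in cm from the true midline. The sign rule is "Leftward errors will be indicated with negative numbers and rightward errors will be indicated with positive numbers". The neglect cutoff works in both directions: "The cutoff score for unilateral visual neglect will be considered as an error of more than 1.4 cm left or right".

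**Who is eligible.** The Inclusion Criteria list "Hemiparesis (right or left" as eligible. The literature review accepts that "the deficit may be observed on the ipsilesional side as well as among subjects with the left brain damage". Dummy Table 1 tabulates side of involvement as right or left.

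**Letter cancellation (LCT).** The Inclusion Criteria define neglect as "an asymmetry between the Letter cancellation task omissions in the contralesional (left) and ipsilesional (right) visual field", with a threshold of 2 letters. The test description places the targets as "20 in the contralesional and 20 in the ipsilesional visual field, respectively left and right". Dummy Table 2 has one row for Right and one for Left, each with a maximum of 20.

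**Analysis.** Data Analysis plans a repeated-measures two-way ANOVA (time within, group between) with the pre-intervention score as covariate. It states no absolute value, lesion-side recoding or side term. Dummy Table 3 has a single LBT row, labelled for the right, reported as mean and SD with a maximum of 20.

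**Sample size.** Box 1 is built on LBT: mean difference 8.6, SD 10.6, alpha 0.05, beta 0.1, 37 per group.

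**The concern.** A patient who neglects the left side tends to mark lines too far right and scores positive. A patient who neglects the right side scores negative. Improvement moves both toward zero, so it lowers the first score and raises the second. A group mean of page-signed scores sets these improvements against each other. In a mixed sample the estimated treatment effect on LBT is pulled toward zero, on the very measure that sizes the trial.

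The letter cancellation fault is related but different. Contralesional means left only after a right-hemisphere lesion. For a right-hemiparetic patient the contralesional field is the right one, so the eligibility wording, the test description and the Table 2 rows do not fit that patient.

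**Working it through.** **Inputs.** From Box 1: difference 8.6, SD 10.6 (units not stated), alpha 0.05 (two-sided assumed), beta 0.1, 37 per arm. Assumption: p, the share of patients who neglect the right side, which the documents do not give.

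**Step 1: the plan's own figure.** n per arm = 2 × [10.6 × (1.960 + 1.282) / 8.6]² = 31.9, so 32 (33 with a t-test). The stated 37 does not reproduce at the stated alpha and beta. It exceeds the required number, so this mismatch is not itself a loss of power. Power with 37 is about 94%.

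**Step 2: the signed contrast.** Let D be the true effect when every score is coded toward the lesion side. Left-neglect patients (share 1 − p) contribute +D and right-neglect patients (share p) contribute −D:

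signed contrast = (1 − p)D − pD = (1 − 2p)D

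This factor needs no unit and no SD.

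**Step 3: power with the SD held at 10.6.** Standard error = 10.6 × √(2/37) = 2.46. Power ≈ Φ[8.6(1 − 2p)/2.46 − 1.96].

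**Step 4: baseline adjustment.** An illustrative simulation assumed baseline error 3 cm (SD 1.2), a follow-up mean of 0.8 × baseline in controls and 0.4 × baseline in the experimental arm (50% lower), residual SD 1.5, 37 per arm and 1,500 runs. Both analyses adjust for baseline.

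| p | Signed contrast | Power, step 3 | n per arm for 90% | Simulated power, signed | Simulated power, side-coded |
|---|---|---|---|---|---|
| 0 | 8.60 | 94% | 32 | 93% | 93% |
| 0.1 | 6.88 | 80% | 50 | 75% | 92% |
| 0.2 | 5.16 | 55% | 89 | 51% | 92% |
| 0.3 | 3.44 | 29% | 200 | 27% | 91% |
| 0.4 | 1.72 | 10% | 799 | 10% | 91% |
| 0.5 | 0 | none beyond alpha | none | 5% | 91% |

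In this simulation the adjusted effect fell from 1.216 cm at p = 0 to 0.744 cm at p = 0.2, a ratio of 0.61 against 1 − 2p = 0.60. Adjustment therefore does not restore the contrast. What it can remove is some of the extra spread that mixing creates: if the side-coded mean is m, the signed variance rises by 4p(1 − p)m², which step 3 leaves out. A second simulation (43 per arm, correlation 0.6, mean deviation 1.5 SD) gave 74% at p = 0.2 with adjustment, against 99% side-coded. Without adjustment it gave 27% to 49% for mean deviations of 1 to 2 SD. Recovery is partial.

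**Step 5: letter cancellation.** Omissions are unsigned counts. If the benefit falls in the neglected field, the Left row carries (1 − p) of the effect and the Right row carries p. Borrowing the LBT standardised effect (8.6/10.6 = 0.81) purely as illustration, power with 37 per arm is 80% in the Left row and 10% in the Right row at p = 0.2, and 41% in each at p = 0.5.

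**Step 6: Table 3.** A mark on a 20-cm line is at most 10 cm from the midpoint. A maximum of 20 and a single row for the right do not match a signed error taken over three lines.

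**The case against.** **The sample may be nearly all left neglect.** The literature review says neglect usually follows right brain damage, the eligibility wording writes left for contralesional, and Figures 1 and 2 show left-hemiparetic subjects. With small p the loss is small: the second simulation keeps 94% adjusted power at p = 0.1, above the planned 90%. This stands as a limit on size. It does not remove the fault, because the same inclusion list admits right hemiparesis and nothing caps p.

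**The power figures are soft.** This also stands. The units of 8.6 and 10.6 are not stated, and a mean deviation of 1.5 SD would be 15.9 if the unit were cm, beyond the 10 cm limit. Only the factor 1 − 2p is firm.

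**The derivation may be left to an analysis plan.** How three errors become one score could be settled in a statistical analysis plan that is not shown. But the protocol itself fixes the sign rule, the model and the page-side table rows, and together these conflict with its eligibility rule.

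**Stronger readings.** A reader might infer that treatment effects cancel in both neglect outcomes, or that an effective treatment must show no difference. The documents do not support either. Letter cancellation has no sign to cancel, and full cancellation of LBT needs p = 50%. For left-neglect patients the signed score does track severity.

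**Conclusion.** The point holds for line bisection. Page-side signing, eligibility of both hemiparetic sides and an uncorrected comparison of means shrink the LBT contrast to (1 − 2p) of its true size. Under the protocol's own inputs this takes power from about 94% to 80%, 55% and 29% at p = 0.1, 0.2 and 0.3. Those figures assume a two-sided test, a fixed SD, neglect contralateral to the lesion and equal benefit on both sides. Since p is unknown, they show sensitivity and do not forecast the result.

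For letter cancellation the finding is narrower: wrong labels for right-hemiparetic patients, and an effect split over two rows. The Table 3 label and maximum are separate errors in the table shell, to be corrected in the same edit.

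**What to change.** 1. **LBT.** Keep the raw signed errors. Analyse the mean over the three lines, in cm, coded positive toward the ipsilesional side (reverse the sign for right-hemiparetic patients). Apply the same coding to the baseline covariate.
2. **Sensitivity analysis.** Lesion-side coding leaves the opposite sign on patients with ipsilesional neglect, which the literature review acknowledges. Add absolute error, or coding by the side neglected at baseline.
3. **LCT.** Report contralesional omissions, ipsilesional omissions and their asymmetry, the quantity that defines neglect at entry.
4. **Wording.** Reconcile the bracketed left and right in the Inclusion Criteria and the LCT description with the eligibility of either hemiparetic side.
5. **Tables 2 and 3.** Relabel the rows to match, and replace the right-only LBT row and its maximum of 20.

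The cost is a change of wording and a recode at analysis. No new data are needed, because side of involvement is already recorded for Table 1.

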**Primary objectives**

- 1. To determine the effectiveness of Task-based and Magnified mirror therapy on Unilateral Spatial Neglect (USN) among post-stroke hemiparetic subjects
  2. To determine the effectiveness of the protocol on motor recovery of the subjects

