**Hypothesis:**

1. Task-based and Magnified Mirror therapy protocol for the paretic upper limb provided for 2 months will decrease the Unilateral spatial neglect by 50% in 1 to 36 months post stroke subjects with hemiparesis when compared with the conventional management.
2. Task-based and Magnified Mirror therapy protocol for the paretic upper limb provided for 2 months will enhance the motor recovery by 30% in 1 to 36 months post stroke subjects with hemiparesis when compared with the conventional management.

**Design***:* Randomized controlled, single blinded trial

**Setting:** Neuro-Rehab Laboratory*,* Department of Occupational Therapy, Pt. Deendayal Upadhyaya National Institute for Persons with Physical Disabilities, New Delhi

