**Sample size:**

The power calculation was done using the values *(Box 1)* for USN assessment from a study on mirror therapy for USN.[^27^](#_ENREF_27) Considering the beta = 0.1 and α = 0.05, the calculation inferred that 37 subjects in each group would be sufficient to detect the desired change. However, to compensate possible drop outs (15%), 43 subjects in each group will be enrolled. Thus, the total sample size will be **86**.

*Box 1*

| Study | Primary measure | Values used | Alpha | Beta | Estimated sample size each group | Total sample size |
| --- | --- | --- | --- | --- | --- | --- |
| *Pandian JD et al*[*^27^*](#_ENREF_27) | Line Bisection Test | Mean difference = 8.6  SD = 10.6 | 0.05 | 0.1 | 37 | 74 |

**Group Allocation and Concealment:** The subjects will be randomly allocated between the experimental and control groups in block of 10. The assessor will be unaware about the group allocation of the subjects and will apply the outcome measures both pre- and post intervention. The randomization process will be conducted by an office staff, not associated with the study, using the SPSS Version 23 software. The intervention will be allocated in the ratio of 1:1. The assignment will be serially arranged in sealed opaque envelopes. The subjects will also be blinded to the purpose of the experimental intervention.

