**Data Analysis:**

The data will be analyzed by using IBM SPSS version 23.0. The demographic and baseline features of the study participants will be analyzed in form of mean (SD) / median (IQR) / n (%) and appropriate test [(Mann-Whitney U (U) / independent t (t) / chi-square (χ^2^)] tests will be used to analyze the difference for the characteristics between the groups. For inferential statistics, an intention-to-treat analysis method will be used by carrying forward the last observation. A repeated-measures 2-way ANOVA (continuous data; within factor, time; between factor, group) will be used to study difference for the post intervention and follow-up scores between the groups. The pre-intervention score will be considered as the covariate with group as the independent variable and posttest score as the dependent variable. The significance level will be set at *P*<.05. The dummy tables to represent the findings are provided below -

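### The protocol names two different leading neglect outcomes (Line Bisection in the sample size, Letter Cancellation in the outcome section), adds the Fugl-Meyer as a third primary, and tests all at 0.05 with no deciding rule

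*Protocol*

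**What the plan says.** - **Sample size, Box 1 (Protocol).** The column for the primary measure holds one entry, "Line Bisection Test | Mean difference = 8.6", with SD 10.6, alpha 0.05 and beta 0.1. It gives 37 per group, raised to 43 for 15% dropout. No time point is given, and no other outcome has a calculation.
- **Outcome measures (Protocol).** Under "Primary measures" the LBT comes first and the LCT second. The LCT entry says that this test "will be the main outcome measure to assess USN". The FMA follows under the same heading; the secondary measures start only after it.
- **Primary objectives and Hypothesis (Protocol).** Neglect and motor recovery are both primary. The second objective is "To determine the effectiveness of the protocol on motor recovery of the subjects", and the second hypothesis is that the therapy "will enhance the motor recovery by 30% in 1 to 36 months post stroke subjects".
- **Data Analysis (Protocol).** "The significance level will be set at *P*<.05" is the only decision rule stated.
- **Dummy Tables 2–4 (Protocol).** Eight rows carry F and P-value columns: LCT right, LCT left, LBT, FMA total, FMA-UE, FMA-UA, FMA-WH and FMA-LE. Week 8 and week 12 both appear, and neither is named as the primary time.

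**The concern.** Two sections give different answers to the question of which neglect test leads, and a third instrument shares the primary heading. With one flat significance level and no rule for a positive trial, nothing in the protocol prevents the primary claim from resting on whichever test reaches P<.05. Two properties that the protocol appears to offer would then not hold. The 5% error rate would apply to each test but not to the overall claim. The 90% power would apply to the LBT but not to the test called the main one, nor to motor recovery.

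**Working it through.** **1. The plan's own figure.** Inputs from Box 1: difference 8.6, SD 10.6, alpha 0.05 (taken as two-sided, since the protocol does not say), power 0.90.

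n per group = 2 × [SD × (z₀.₉₇₅ + z₀.₉₀) / difference]² = 2 × [10.6 × (1.960 + 1.282) / 8.6]² = 31.9, so 32; the exact t-test gives 33.

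The stated 37 is not reproduced from these inputs. At 37 per group the t-test power is 93%, so the LBT is not short of patients if Box 1 is taken at face value. The dropout step does reproduce: 37 × 1.15 = 42.6, so 43.

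**2. Do the Box 1 inputs fit the outcome?** The LBT section measures error in centimetres from the midpoint of 20-cm lines, so a mark on the line is at most 10 cm off. A signed error between −10 and +10 has a standard deviation of at most about 10, and an SD of 10.6 does not fit that scale. The values may be in another unit, or a sum or change score; the protocol does not say. The literature review describes the source trial's result at 6 months, whereas this trial assesses at weeks 8 and 12.

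**3. Familywise error if any one significant result supports a claim.** The chance of at least one P<.05 with no true effect is 1 − 0.95^k for k independent tests. For correlated tests it was simulated with multivariate normal statistics. The protocol gives no correlations, so those below are assumptions.

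| Family | Independent | r = 0.3 | r = 0.5 | r = 0.7 |
|---|---|---|---|---|
| LBT and LCT (k = 2) | 1 − 0.95² = 9.75% | 9.5% | 9.1% | 8.3% |
| LBT, LCT and one FMA score (k = 3) | 1 − 0.95³ = 14.3% | 13.7% | 12.5% | 10.9% |

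At r = 0.9 these fall to 7.1% and 8.4%, still above 5%.

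**4. All eight table rows.** The formula gives 1 − 0.95⁸ = 33.7%, but the rows cannot be independent: FMA-UE (66) = UA (36) + WH (30), and FMA total (100) = UE + LE (34). The simulation built these sums in, with component SDs proportional to the maximum scores.

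- All component scores uncorrelated: 29.0%. The nesting alone brings the figure below 33.7%.
- Correlation 0.3–0.7 among the three neglect scores, 0.5–0.85 among the three FMA components and 0–0.3 between the two domains: about 19–25%.
- Strongest correlations tried (0.7, 0.85 and 0.3): 18.6%.

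The range is therefore roughly 18–29%, counting one P value per row.

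**5. Price of an equal split.** LBT power at two-sided alpha 0.05/3 = 0.0167 with standardised difference 8.6/10.6 = 0.811 (t-test) is 85% at 37 per group and 90% at 43 per group. The lower figure is the relevant one if the anticipated 15% are lost. The protocol's carrying forward of last observations keeps 43 in the analysis, but may dilute the effect.

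**The case against.** The LBT is the first item under the primary heading, so the trial is sized on a declared primary, and sizing on one of several primaries is no error in itself. The sentence that calls the LCT the main measure is visibly garbled. Multiplicity rules are often left to a statistical analysis plan, which is not available here. The 0.05 level is a nominal level; no section says that a single significant result makes the trial positive. The dummy tables show how results will be presented and do not declare eight endpoints. If neglect and motor recovery each support their own claim, the neglect family has only two tests.

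Much of this stands, and it limits the size of the point. It does not remove the contradiction between Box 1 and the LCT entry, which is in the protocol itself. Nor does it supply a success rule. If all primaries had to succeed, alpha would not be inflated, but the protocol does not say so, and power for joint success is not calculated.

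A reader might infer three stronger things that the documents do not support:

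- **That the false-positive rate is 33.7%.** The nested FMA scores rule this out.
- **That the inflation is certain.** It depends on an any-one-result reading, which the protocol neither states nor excludes.
- **That the sample size supports the LBT at 8 weeks.** Box 1 gives no time point, and its values do not fit the centimetre scale.

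**Conclusion.** The point holds as a contradiction over the primary outcome, together with a testing rule that leaves the deciding result open. The stated 90% power belongs to the LBT only, and no power is shown for the LCT or the FMA. If one significant primary result is enough, the familywise error is about 8–10% for the two neglect tests, 11–14% for the three instruments and roughly 18–29% for the eight rows. The first two ranges assume correlations from 0 to 0.7; the third also depends on the assumed structure in the working. The two- and three-test figures are the firmer ones, because they do not require each FMA subscore and each LCT side to count as a primary endpoint.

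**What to change.** 1. Name one primary endpoint and one primary time point, and make Sample size, Outcome measures, Data Analysis and dummy Tables 2–4 agree. Remove the claim to be the main or primary measure from whichever neglect test is not chosen.
2. If the LBT is chosen, first reconcile 8.6 and SD 10.6 with the centimetre scale, and state the time point they refer to. If the LCT is chosen, give its own calculation, or state that the 90% power does not apply to it.
3. Prespecify one score per instrument. Test the remaining primary instruments in a fixed order at 0.05, stopping at the first non-significant result, or use Holm across the three. Report the other FMA and LCT scores as secondary or descriptive.
4. Do not describe motor recovery as powered, nor the LCT unless it is given its own calculation.

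**Cost.** Naming the primary and the order is a change of wording. Moving to the LCT needs a new calculation, and a single LCT score such as left–right asymmetry would be a new analysed endpoint, since Table 2 shows the two sides separately. With a fixed order, later outcomes can be claimed only if the earlier ones succeed. An equal split at 0.05/3 leaves LBT power at 85% with 37 per group and 90% with 43, taking Box 1 at face value.
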